### Procedure

#### Recruitment, randomisation and allocation

A diagram of the study design is shown in Fig. 1. Participants will be recruited from medical services and chronic illness networks; social media and online communities across Australia. Interested participants will be directed to a website which will outline study eligibility and will contain a link to the online consent form and screening measures. Participants who meet inclusion criteria will be randomly assigned a participant code, in order to link data across time points while preserving anonymity. They will proceed to an online pre-test questionnaire which will gather demographic and health resource use data (re-administered at post-test and follow-up), as well as the outcome measures. To promote retention participants will be informed that they will receive AUD$20 after completing the post-test surveys, and an additional $20 after they have completed the follow-up surveys. Participants will also be able to opt-in to receive a copy of the study results via email.

**Fig. 1 Fig1:**
[figure not shown]
An overview of the Study Design

Following completion of the pre-test, participants will be randomised to conditions using the Qualtrics randomiser function. Participants in both arms of the trial will be contacted by a research assistant shortly after completing the baseline survey, who will inform them of their condition allocation, reiterate study procedures and answer any questions: as participants are recruited on a rolling basis, those assigned to SCO-CMC will receive access to the program as soon as the research assistant has made contact with them. At four and 12 weeks after completing baseline measures, all participants will be sent an email asking them to complete the outcome measure battery again. Following completion of the third set of measures, participants in the WLC will be contacted by the research assistant, who will provide a code for program access. All participants will receive up to two reminders to complete the measure battery at each time point; participants enrolled in the intervention will also receive an email or text reminder 2 weeks post enrolment to encourage them to continue progressing through the program.

#### Qualitative data collection and analysis

At baseline, participants will be randomly selected to be invited to participate in a telephone interview to discuss their experience of participating in the SCO program: participants will be invited to participate in the interview following the third assessment point. Forty participants will be randomly selected at baseline and invitations will be issued until ten interviews are complete. Baseline selection is designed to ensure that interviewed participants include those who may have disengaged from the program. Interviews will be conducted by the research assistant and will explore the impact of the SCO-CMC program on the lived experience of young people with CMCs, identify potential mechanisms of change not assessed in quantitative measures, and gather data on potential iatrogenic effects. Interviews will also be used to gather detailed information on program satisfaction and feedback regarding potential revisions. Finally, qualitative data will also be collected by the online program (i.e. in the interactive exercises which use digital forms for participants to complete exercises). We will conduct thematic analysis of this data to identify key themes regarding program benefits, challenges, and application of program strategies to participants’ lived experience.

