### Participants

Participants will be *N* = 96 Australian adolescents and young adults (48 per group), aged between 16 and 25 years, who self-report a current diagnosis of a CMC (for example arthritis, asthma, cancer, cystic fibrosis, diabetes, epilepsy, haemophilia, IBD, lupus, multiple sclerosis, and myalgic encephalomyelitis). Additional inclusion criteria are as follows (1) Australian resident; (2) fluent English speaker; (3) regular access to the Internet; (4) able to access online video and audio content.

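### Random selection at baseline does not ensure that disengaged users are interviewed when invitations stop at ten completed interviews, and the text does not say which arm is sampled

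*Protocol article*

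**What the plan says.** The interview plan is in the protocol article under Qualitative data collection and analysis.

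- Who is chosen, when, and what they will discuss: "At baseline, participants will be randomly selected to be invited to participate in a telephone interview to discuss their experience of participating in the SCO" (the online training).
- How many: "Forty participants will be randomly selected at baseline and invitations will be issued until ten interviews are complete".
- Why at baseline: "Baseline selection is designed to ensure that interviewed participants include those who may have disengaged from the program".
- When they are invited: "participants will be invited to participate in the interview following the third assessment point".

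Two statements under Recruitment, randomisation and allocation bear on this. Allocation comes after the baseline questionnaire: "Following completion of the pre-test, participants will be randomised to conditions using the Qualtrics randomiser function". And once the third set of measures is complete, "participants in the WLC will be contacted by the research assistant, who will provide a code for program access".

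The article does not name the arm from which the forty are drawn, and it reserves no interviews by level of engagement. The Discussion is more cautious than the Methods: it presents the interviewing of dropouts only as a possibility.

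**The concern.** There are two separate points.

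**Stopping rule.** A random list of forty made at baseline is not filtered by later engagement, and that is a sound start. The interviewed sample, however, is the subset of that list who agree before the tenth interview is done. The list allows up to 30 people not to be interviewed and still meets its target. Nothing in the rule ties the final ten to the list's engagement profile, so the stated purpose does not follow from the procedure.

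**Sampling frame.** The draw is of participants, without an arm. Waitlist members receive access only after the assessment that also triggers the interview invitation. If they are in the draw and are interviewed at that point, they have no program experience to describe.

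The Aims section makes interviews the means of judging satisfaction and acceptability. The interview section also relies on them for possible iatrogenic effects, unmeasured mechanisms and revisions to the program. Users who stopped are an obvious source on poor fit and harm. With only ten interviews, the absence of one or two such people changes what can be said.

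**Working it through.** **Inputs from the article**

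- Participants: 96 in total, "Australian adolescents and young adults (48 per group), aged between 16 and 25 years".
- Interviews: 40 selected, 10 completed. These are quotas with no calculation behind them, so there is no figure to reproduce for the interviews themselves.
- Sample size: 40 per group, typical dropout of about 15–20%, target 48 per group. Check: 40/(1 − 0.15) = 47.1, rounded up to 48; 40/(1 − 0.20) = 50. The target of 48 matches the 15% end.

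**Assumptions**

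- Dropout *d* = 0.15 to 0.20 stands in for disengagement. The article gives no separate disengagement rate.
- *r* is the acceptance of disengaged users relative to engaged users. The article gives no acceptance rate, so *r* = 1, 0.5 and 0.25 are shown as a range.

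**Step 1. Draw from the program arm only**

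The share of disengaged users among those who accept is s = d·r / (d·r + 1 − d). The chance of none in ten is (1 − s)^10, and the expected number is 10·s.

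| r | s (d = 0.15; 0.20) | Expected in ten | Chance of none |
|---|---|---|---|
| 1 | 0.150; 0.200 | 1.5; 2.0 | 0.20; 0.11 |
| 0.5 | 0.081; 0.111 | 0.81; 1.11 | 0.43; 0.31 |
| 0.25 | 0.042; 0.059 | 0.42; 0.59 | 0.65; 0.54 |

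Example, d = 0.15 and r = 0.5: s = 0.075/(0.075 + 0.85) = 0.081, and 0.919^10 = 0.43.

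This formula treats the ten as independent draws. Sampling ten of 48 without replacement lowers the equal-acceptance figures somewhat. With 7 disengaged users among 48, C(41,10)/C(48,10) = 0.17; with 10 among 48, C(38,10)/C(48,10) = 0.07. The conclusion is the same.

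If disengagement is more common than dropout, the risk falls. At an assumed d = 0.40, the chance of none is 0.006, 0.06 and 0.21 for the three values of *r*.

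**Step 2. Draw from both arms**

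With 48 of 96 on the waitlist and equal acceptance, 40 × 48/96 = 20 of those selected and 10 × 48/96 = 5 of those interviewed are expected to be waitlist members. The hypergeometric 95% range for the interviewed is 2 to 8, and the chance of three or more is 0.95. If waitlist members accept half or a quarter as often as program users, their expected share is 0.5/1.5 = 33% or 0.25/1.25 = 20%.

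The share of disengaged program users is then q = 0.5·d·r / (0.5·d·r + 0.5·(1 − d) + 0.5). At r = 1, q is 0.075 to 0.10, which gives 0.75 to 1.0 expected in ten and a chance of none of 0.46 to 0.35. At r = 0.5 the chance of none is 0.67 to 0.58.

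**Step 3. What naming the arm achieves**

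Limiting the draw to SCO-CMC removes the waitlist problem, but it leaves the Step 1 probabilities as they stand. Only a reserved place or a separate invitation list changes those.

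**The case against.** The strongest reply is that the article already points to program users. The Aims section speaks of interviewing those who took part, the interview topic is experience of the program, and the Discussion refers to people who drop out of it. A person never given access can do none of these things. Forty drawn from the 48 in SCO-CMC fits that text. Waitlist members could also be interviewed later, after access, since no latest date is set. This stands. A reader might infer from the unqualified word participants that about half of the interviewees will be non-users. The documents do not support that as the expected outcome; it is what follows if the draw is run on both arms. What remains is an ambiguity. The recruitment section does name the arm when it means only one, and the interview section does not.

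A reader might also infer that disengaged users will probably be missed. The figures do not show that. In a program-arm draw with equal acceptance, at least one is interviewed with a chance of about 80–89%. The chance of none passes one half only if they accept about a quarter as often (program arm) or half as often (both arms), and the documents support neither ratio. That engaged users accept more readily is plausible, but the article does not state it.

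The reply is also right that interviews are not the only source. Log-ins, time in program, module completion, attrition and in-program responses are collected as well. The component is exploratory and small, and random selection at baseline is a legitimate way to avoid sampling only completers. None of this rescues the claim to ensure inclusion, which fails even at equal acceptance.

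**Conclusion.** The point holds in limited form. Baseline selection with a stop at ten completed interviews makes it possible, but not assured, that disengaged users are interviewed. With 15–20% dropout as the proxy, the chance of none in ten is about 11–20% for a program-arm draw with equal acceptance. It is 31–43% under the assumption that disengaged users accept half as often. The first range rests on the proxy and on independent draws; the second also rests on the assumed acceptance ratio.

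Separately, the sampling frame should be stated. The program-arm reading is the more natural one. Under a two-arm draw with equal acceptance, about 5 of 10 interviewees would have had no program access up to the third assessment.

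The consequence is confined to the interview findings on acceptability, mechanisms and possible iatrogenic effects. The efficacy, mediation and cost-utility analyses are not touched.

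**What to change.** 1. State that interviewees are drawn from the SCO-CMC arm, after allocation, or that waitlist members are interviewed only after they have used the program.
2. Reserve a minimum number of the ten places for low-engagement users, defined in advance by the number of modules completed. Module completion is already listed under Program engagement and adherence.
3. If those places do not fill from the random list, invite all low-engagement users in the arm.
4. Report how many were invited and how many were interviewed in each engagement group.
5. If the places are not reserved, replace the claim to ensure inclusion with the more cautious expectation given in the Discussion.

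The cost is a sentence or two in the protocol, a sorted invitation list and a few more invitations. Some reserved places may stay empty, so the minimum should be modest. For illustration, if 30% of the 48 disengaged and 20% of those accepted (both assumed), 48 × 0.3 × 0.2 = 2.9 acceptors would be expected, too few for five fixed places. Unfilled places, reported as such, would still show readers how far the interviews reached this group.

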#### Data monitoring, management, and post-trial care

No data monitoring committee will be engaged given that the intervention is low risk and participants are able to access care as usual while participating. Interim analyses will not be conducted. Study investigators will permit trial-related audits in line with Curtin University Human Research Ethics Committee requirements and approvals. Protocol amendments will be submitted to the Curtin University Human Research Ethics Committee, and, if approved, communicated to participants via email.

A research assistant will be engaged to ensure blinding of the data analyst to group allocation, and data will be managed in line with Curtin University data management guidelines. Participant email addresses will not be stored with any of the trial data. Participants will be encouraged to liaise with the research assistant if they wish to withdraw from the trial or if they wish to be directed to additional psychological support at any point. Information about free online and telephone-assisted psychological support is also provided to participants on the participant information sheet, and within the SCO-CMC program.

### Statistical analysis

#### Tests of intervention effects

We will perform Intention to Treat and Per Protocol analyses, conduct a sensitivity analysis [39], and compare complete cases versus cases lost to follow-up on baseline characteristics and scores on clinical measures, by randomisation group [64]. GLMM Mixed Model Repeated Measures will compare change in outcome measures across conditions, and time points, while controlling for random effects including age and gender. The group*time interaction will be calculated as a test of intervention effects. Using DASS-21 scores participants will be classified into outcome categories (Recovered, Improved, Unchanged, Deteriorated) according to Reliable Change Index and Clinical Significance of change at post-treatment and follow-up [32], to determine whether the SCO-CMC and control groups differ in clinically significant treatment outcome over time (Cochrane’s Q).

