### Outcome measures

#### Psychological distress

Psychological distress over the past 30 days will be measured using the Kessler 10-item psychological distress scale (K-10 [36];). The K10 is a self-report measure comprising 10 items on a 5-point scale. Total scores range from 10 to 50; scores above 15 indicate moderate to severe psychological distress, while scores greater than 20 indicate higher likelihood of mental disorder [1].

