#### Self-compassion

Self-compassion will be measured using the Short Form of the Self-Compassion Scale (SCS-SF [50];). This self-report scale consists of 12 items designed to measure the six subcomponents of self-compassion: mindfulness, overidentification, common humanity, isolation, self-kindness (e.g. “I try to be understanding and patient towards those aspects of my personality I don’t like”) and self-judgement; each item is rated on a 5-point scale. Item scores are used to generate a total self-compassion score, which has a high correlation with the total score of the long form Self-Compassion Scale [50]. Psychometric studies have demonstrated the reliability and validity of both forms of the Self-Compassion Scale with adolescents and young adults.

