#### Emotion regulation difficulties

Emotion regulation difficulties will be measured using the Difficulties in Emotion Regulation Short Form (DERS-SF), a widely-used 18-item measure of emotion regulation problems [35]. This self-report scale measures difficulties with emotion regulation along six dimensions: (1) awareness of emotions; (2) emotional clarity; (3) acceptance of emotions; (4) access to emotion regulation strategies; (5) ability to engage in goal-directed behaviour when experiencing negative emotions; and (6) impulse control in the face of difficult emotions. The DERS-SF provides a total scale score for emotion regulation difficulties and is a valid and reliable measure of difficulties with emotion regulation in both adolescents and adults [35].

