#### Coping

Coping will be measured using the brief COPE [11], a 28-item self-report measure of coping strategies which is a short version of the original COPE scale. Respondents rate items (e.g. “I take action to try to make the situation better”) across 14 subscales, using a 4-point scale. The subscales can be categorised into those representing approach coping (active coping, emotional support, use of informational support, positive reframing, planning, and acceptance) and those representing maladaptive coping (denial, self-distraction, substance use, venting, self-blame, and behavioural disengagement) subscales. Avoidant coping has been associated with poor physical health outcomes in adults with chronic medical conditions [18]. The Brief COPE has good internal reliability [11] including among adolescent samples [30].

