#### Wellbeing

Wellbeing will be measured using the World Health Organization Wellbeing Index (WHO-5), a widely-used, validated measure of subjective wellbeing designed for use in clinical trials [62]. The WHO-5 measures positive psychological well-across 5-items using a 6-point scale, and scores are used to obtain a percentage score ranging from 0 to 100. The WHO-5 displays acceptable psychometric properties among adolescents [7] and adults [6].

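### The responder and deterioration classification uses DASS-21 scores, but the article neither lists nor schedules the DASS-21; the only distress scale listed is the K-10

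*Protocol article*

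**What the plan says.** Under Tests of intervention effects, after the mixed model and its group-by-time interaction, the article adds a responder analysis: "Using DASS-21 scores participants will be classified into outcome categories (Recovered, Improved, Unchanged, Deteriorated", the classification to be made "according to Reliable Change Index and Clinical Significance of change at post-treatment and follow-up". The two arms are then to be compared on these categories with a test that the article calls Cochrane's Q, read here as Cochran's Q.

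Under Outcome measures, the distress construct is assigned to a different instrument: "Psychological distress over the past 30 days will be measured using the Kessler 10-item psychological distress scale". That section gives the K-10 total range as 10 to 50 and mentions two thresholds: above 15 for moderate to severe distress, and greater than 20 for a higher likelihood of mental disorder.

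Under Procedure, the pre-test questionnaire holds demographics, health resource use and the outcome measures. The outcome battery is sent again at 4 and 12 weeks.

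**The concern.** The analysis section relies on an instrument that the measurement sections do not contain. The classification needs a score on the same scale at baseline and at each later assessment, and no DASS-21 score is documented at any of them.

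The names cannot simply be exchanged. Reliable change and clinical significance both depend on properties of the particular scale, so values that suit the DASS-21 cannot be applied to K-10 totals. If the mismatch is noticed only once the data are in hand, the scale, the reliability value, the SD and the cut-off all become choices made with results in view. The analysis would then no longer be pre-specified.

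The classification is supplementary, but it is the only place where the plan counts individuals who got worse. The article plans no data monitoring committee. Its other route to unwanted effects at the individual level is qualitative, through about ten interviews.

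**Working it through.** No figure in the plan needs reproducing. The check sets the sections side by side.

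**Step 1. What is measured.** The Outcome measures section has eight entries:

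| Construct | Instrument |
|---|---|
| Psychological distress | K-10 ("will be measured using the Kessler 10-item psychological distress scale") |
| Self-compassion | SCS-SF ("Self-compassion will be measured using the Short Form of the Self-Compassion Scale") |
| Emotion regulation difficulties | DERS-SF |
| Coping | Brief COPE ("Coping will be measured using the brief COPE") |
| Wellbeing | WHO-5 |
| Quality of life | AQoL-6D |
| Health resource use | study-specific questionnaire |
| Engagement and adherence | program metrics and self-reported practice |

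The DASS-21 is none of the eight. Its single mention in the article is in the analysis section.

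**Step 2. What is scheduled.** There are three assessments: baseline, 4 weeks and 12 weeks. Each is described as containing the outcome measures and resource use, with demographics at baseline. The text schedules the DASS-21 at 0 of 3.

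**Step 3. What the classification needs.** In its usual form the Reliable Change Index is

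RCI = (later score − baseline score) / S_diff, with S_diff = SD × √(2 × (1 − r)),

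where SD and r are the standard deviation and reliability of the scale used. Clinical significance also needs a cut-off on that scale. Every term is therefore specific to the instrument, and baseline, post-treatment and follow-up scores must all come from it. With no documented DASS-21 scores, none of the four categories can be assigned from the listed data.

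**Step 4. Is the K-10 a ready substitute?** It is scheduled at all three assessments, so its data would exist. The cut-off would still be open. A total above 15 means 16 or more, and a total greater than 20 means 21 or more. The two rules disagree for totals of 16, 17, 18, 19 and 20, which is five score values. A participant moving from 22 to 18 crosses one threshold and not the other, so the choice can change who counts as Recovered.

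**Step 5. Would the between-arm test then run?** Cochran's Q compares proportions of a binary response across related samples, such as the same people under several conditions. Here there are two independent arms and four categories. Changing the scale alone would not make the named test suitable.

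**The case against.** The strongest reply is that this is a naming slip in a secondary analysis. The article calls the trial exploratory. Its stated test of intervention effects is the group-by-time interaction. The sentence giving the primary aim names self-compassion, emotion regulation and coping, not distress. No sample-size, mediation or cost-utility result rests on the DASS-21. All of this stands, and it limits the importance of the point.

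A second reply is that the DASS-21 may be collected but not mentioned. The study-design figure is not available in the text reviewed, and the screening measures completed before randomisation are unnamed. A reader might therefore infer that the trial never collects the DASS-21, but the text supports only that it is not listed or scheduled. Even so, a scale given once at screening could not supply post-treatment and follow-up scores, so the gap remains.

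A third reply is that such detail belongs in a statistical analysis plan. That is fair for the reliability value, the SD and the denominator for Recovered: someone starting below the cut-off cannot recover under any such scheme, and this is not an error. It does not answer a contradiction between two sections of the same article.

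Three other stronger readings should be set aside:

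- A reader might infer that the plan's only quantitative sign of harm is lost. The mixed model on the K-10 would still show mean worsening by arm. Only the count of individuals who deteriorate is lost.
- A reader might infer that no participant can ever be classified. That treats non-collection as established, which it is not.
- A reader might infer from the K-10's 30-day recall that the 12-week classification should be the main one. That is a separate matter. It depends on assumptions about how quickly an effect builds and when access starts, which the article does not supply.

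**Conclusion.** The inconsistency is real, and nothing in the article resolves it. One planned analysis, at both of its time points, has no documented input data, and the test named for comparing the arms does not suit the design. The effect is confined to this supplementary classification; the group-by-time tests, mediation and cost-utility analyses stand as they are. The point should be fixed before data are seen, but it does not put the trial's main conclusions at risk.

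The conclusion rests on the article's text being a complete list of repeated measures, apart from the missing figure, and on Cochran's Q being the test meant. If the full protocol schedules the DASS-21 at all three assessments, the fault reduces to an omission from the outcome list plus the unsuitable test.

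**What to change.** Reconcile the Outcome measures and Statistical analysis sections before data are seen, by one of two routes:

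1. **Name the K-10 in the classification sentence.** State the K-10 reliability and SD for the Reliable Change Index, and choose a single cut-off for clinical significance, since the article mentions two. This needs no new data.
2. **Add the DASS-21** to the outcome measures and to the baseline, 4-week and 12-week assessments, with its own reliability, SD and cut-off. This lengthens the questionnaire at all three assessments. It cannot supply baseline scores for anyone enrolled before the change; the article does not say whether recruitment had begun.

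The first route is cheaper. The choice belongs to the investigators, who know which scale they intended.

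In the same amendment, replace Cochran's Q with a comparison of the categories between the independent arms at each time point, for example a chi-square or exact test, or an ordinal model if the four categories are treated as ordered. On the first route the total cost is a short paragraph of amended text and its submission to the ethics committee.

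### Entry requires no level of distress, yet Recovered is compared between arms without limiting it to participants who could recover, so the difference is diluted

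*Protocol article*

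**What the plan says.** **Who enters.** Under Participants, eligibility is age 16–25 and people "who self-report a current diagnosis of a CMC", plus practical criteria: "1) Australian resident; (2) fluent English speaker; (3) regular access to the Internet; (4) able to access online video and audio content". No distress score is required. Under Recruitment, randomisation and allocation, the study website "will contain a link to the online consent form and screening measures", but no distress threshold is attached to that screening.

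**Who is classified.** Under Tests of intervention effects, "participants will be classified into outcome categories (Recovered, Improved, Unchanged, Deteriorated) according to Reliable Change Index and Clinical Significance of change", at post-treatment and follow-up, to see whether the arms differ in clinically significant outcome. The passage sets no baseline restriction and has no category for people who were already well.

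**Which scale.** The same sentence begins "Using DASS-21 scores participants will be classified into outcome categories". Under Outcome measures, however, "Psychological distress over the past 30 days will be measured using the Kessler 10-item psychological distress scale", and the DASS-21 is not listed there. For the K10 the protocol gives a range of 10 to 50 and two reference scores: above 15 for moderate to severe distress, and the statement that "scores greater than 20 indicate higher likelihood of mental disorder". It names neither as the cut-off for clinical significance.

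**The concern.** Recovery on a clinical-significance rule means moving from the clinical to the non-clinical range. Someone who starts in the non-clinical range cannot make that move, whichever arm they are in, so they are a structural zero for Recovered. Reliable improvement needs a fall larger than the Reliable Change Index (RCI), and someone close to the scale floor has no room for one. On the K10, a participant who enters at 12 can fall by 2 points at most. A person who was well and stayed well is then coded Unchanged, the same code as a distressed person who did not respond.

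Two things follow for the comparison of Recovered. The difference is scaled down by the share of participants who were distressed at baseline. And with about 40 completers per arm, that share can differ noticeably between arms by chance, which moves the two Recovered rates for reasons unrelated to the program.

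**Working it through.** **Plan's own figure.** The protocol gives no expected rate or power for this classification, so there is nothing to reproduce. Its sample size of 40 completers per group is used below only as the arm size.

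**Step 1: dilution.** Let q be the share in the clinical range at baseline, and p1 and p0 the recovery rates among those participants. The whole-sample rates are q·p1 and q·p0, so the expected difference is q·(p1 − p0). With assumed rates of 40% and 15%, q = 1 gives 0.25 and q = 0.5 gives 0.125.

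**Step 2: how large 1 − q might be.** The document gives no baseline distribution. Assumption: K10 normal with mean μ = 20 to 25 and SD 8, truncated to 10–50. The share at or below x is [Φ((x−μ)/8) − Φ((10−μ)/8)] / [Φ((50−μ)/8) − Φ((10−μ)/8)].

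- x = 20, μ = 20: (0.500 − 0.106)/(1.000 − 0.106) = 0.44
- x = 20, μ = 25: (0.266 − 0.030)/(0.999 − 0.030) = 0.24
- x = 15, μ = 20: (0.266 − 0.106)/0.894 = 0.18
- x = 15, μ = 25: (0.106 − 0.030)/0.969 = 0.08

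Treating scores as integers (limits moved by half a point) gives 0.48 and 0.27 for x = 20, and 0.21 and 0.09 for x = 15. Across both conventions, about 24–48% could not be Recovered with a cut-off of 20, and about 8–21% with a cut-off of 15. A 20-point difference among the distressed becomes 20 × (0.52 to 0.76), about 10–15 points, or 20 × (0.79 to 0.92), about 16–18 points.

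**Step 3: who can still be Improved.** RCI = 1.96·SD·√(2(1 − r)). With SD 8 and an assumed reliability r of 0.90: 1.96 × 8 × √0.2 = 7.0, so a reliable fall needs a baseline of about 17.0 or more. Over SD 6–9 and r 0.85–0.93 the RCI runs from 4.4 to 9.7, and the minimum baseline from 14.4 to 19.7.

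- Against a cut-off of 20, some sub-threshold participants can be Improved under every combination tried.
- Against a cut-off of 15, this holds only for the most favourable one (SD 6, r 0.93).

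On the step 2 distribution with RCI 7.0, about 13–28% (continuous) or 15–31% (integer) could not show reliable improvement. Truncation reduces the SD to about 6.8–7.4. Using that SD, the RCI is about 5.9–6.5 and the continuous share about 12–22%.

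**Step 4: chance imbalance.** The standard error of the between-arm difference in q is √(2q(1−q)/40). This is 0.112 at q = 0.5 and 0.102 at q = 0.7, so a gap of 10 points or more arises in roughly a third of trials (normal approximation). For illustration, take rates of 40% and 15%. If the shares distressed are 55% and 45%, the difference is 0.55×0.40 − 0.45×0.15 = 0.153. With the shares reversed it is 0.45×0.40 − 0.55×0.15 = 0.098. The balanced value is 0.125.

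**Step 5: what restriction gains.** Power = Φ((d − 1.96·se0)/se1), with se0 = √(2p̄(1−p̄)/n) and se1 = √((p1(1−p1)+p0(1−p0))/n). Here d is the difference in rates, p̄ is their mean, and n is 40 per arm unrestricted or 40q restricted.

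| Rates among distressed | q | Unrestricted | Restricted |
|---|---|---|---|
| 40% v 15% | 0.8 | 0.58 | 0.61 |
| 40% v 15% | 0.5 | 0.37 | 0.42 |
| 40% v 15% | 0.3 | 0.23 | 0.27 |
| 50% v 20% | 0.8 | 0.67 | 0.72 |
| 50% v 20% | 0.5 | 0.42 | 0.51 |
| 50% v 20% | 0.3 | 0.26 | 0.33 |

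The gain is about 3–9 points. Most of the power loss comes from having fewer informative participants, and restriction cannot restore that.

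**The case against.** Several objections have force.

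- **Dilution is not bias.** The program is offered to any eligible young person, and the whole-sample difference in Recovered is a valid intention-to-treat quantity for that population. This stands. The complaint is about interpretation and noise, and the restricted comparison answers a different question.
- **The denominator may be set elsewhere.** The article is condensed, cites a method for the classification, and says explicitly in its cost-utility section when it means everyone. This stands in part. But the article does state who is classified and for what comparison, without limit, beside entry criteria that admit people who are well.
- **The figures are assumed, and on a scale the sentence does not name.** True. The direction follows from logic; the size does not follow from the document.
- **Little rests on this analysis.** The trial is exploratory, and its stated test of intervention effects is the group-by-time interaction. This limits the weight of the point.
- **The sentence has more basic problems.** It names the DASS-21, and it cites Cochran's Q, a test for matched binary responses, for two independent arms. Those need settling first, but settling them would not settle the denominator.

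A reader might go further and infer that participants who are well at baseline can only be scored as failures. The document does not support that. It calls no category a failure, sub-threshold participants far enough above the floor can still be Improved, and Deteriorated is informative for everyone.

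**Conclusion.** The point holds for Recovered. The protocol admits participants at any distress level and compares a recovery category that those in the non-clinical range at baseline cannot enter. The expected difference is reduced by the factor q and carries chance variation in q between arms. For Improved the problem is narrower: it affects only those too near the scale floor.

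The size is not fixed by the document. It depends on the scale, the cut-off and the baseline distribution, none of which is settled. The shares of 24–48% (cut-off 20) and 8–21% (cut-off 15) rest on an assumed K10 mean of 20–25 and SD of 8. The power figures rest on assumed recovery rates.

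It would be tempting to conclude that both Recovered and Improved should be confined to the distressed. That does not follow, because it would discard participants who can show reliable improvement. This is a worthwhile correction to a supporting analysis and does not touch the group-by-time test.

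**What to change.** Amend the classification sentence so that, on the distress scale actually collected and with its cut-off specified in advance:

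1. Recovered is compared between arms only among participants in the clinical range at baseline.
2. Improved (reliable change) and Deteriorated are reported for all randomised participants.
3. The recovery conclusion is stated to apply to the subgroup distressed at baseline.

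The outcome measures are completed before randomisation, so a restriction on the baseline score keeps the randomised comparison intact. Entry criteria do not change.

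The cost is a sentence or two of text, a smaller denominator for Recovered, and a recovery conclusion limited to that subgroup. The return is a rate that describes people who could reach the category, with a modest gain in power.
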